### Aims

The primary objective is overall survival (OS) as predicted by baseline self-reported fatigue severity (European Organisation for Research and Treatment of Cancer Quality of Life Questionnaire-Core 30) independently from other known prognostic factors for OS.

The secondary objectives are:to devise a patient-centric frailty score for RRMM patients;to investigate the prognostic value of the frailty score in the setting of RRMM;to investigate HRQOL over time (outcome measures: EORTC QLQ-C30 and QLQ-MY20) by type of treatment and examine factors that contribute the most in maintaining baseline HRQOL levels;to investigate relationship between satisfaction with information provision (outcome measure: EORTC INFO-25) and HRQOL outcomes (outcome measures: EORTC QLQ-C30 and QLQ-MY20);to assess patients’ preferences for involvement in treatment decision-making and the relationships between preferences and patient characteristics.

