### Statistical considerations

#### Sample size determination

Based on previous evidence in MM patients [13, 14], the EORTC QLQ-C30 fatigue scale was used to calculate sample size and considered as the primary outcome in this study. We performed a calculation in order to detect, at least, a hazard ratio (HR) of 1.11 for overall survival, for each 10-points increase (i.e. worse score) on the baseline fatigue scale, assuming a baseline standard deviation of 29 points [43]. Based on previous studies and on clinical grounds [44], we also assumed a minimum event rate of 35% during the study and considered a follow-up of 30 months from date of enrolment. Allowing for an alpha error of 0.05 and a power of 90%, the calculated sample size for this group is 296 patients. However, estimating an overall 5% of patients not evaluable for whatever reason, the actual sample size required is 312 patients.

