#### Primary outcome analysis

The primary HRQOL objective is to investigate the prognostic value on overall survival of baseline self-reported EORTC QLQ-C30 fatigue scale ratings, independent from the clinically-based prognostic frailty score [6]. Differences between groups will be assessed using χ2, Fisher’s exact, Wilcoxon Mann-Whitney and Kruskall-Wallis tests. We will investigate the prognostic value of baseline variables by Cox proportional hazards regression analysis, including the baseline fatigue score, the prognostic frailty risk groups and established prognostic factors in MM. An extended Cox model will account also for possible time-varying confounding factors (e.g. type of treatment). We will use the likelihood ratio test to assess the prognostic information possibly provided by fatigue, in addition to the prognostic frailty score, by the likelihood ratio test. The robustness of final findings will be assessed by a bootstrap re-sampling procedure [45, 46]. Conditional to the actual prognostic value of the fatigue scale, we will develop a fatigue-adjusted prognostic frailty score included in this scale.

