#### Secondary outcome analyses

The same analysis as described above will be also performed using the remaining scales of the EORTC QLQ-C30 and those of EORTC QLQ-MY20. We will investigate HRQOL profiles by a repeated measures linear mixed model, reporting estimated means, standard deviations (SDs) and 95% confidence intervals. We will assess the clinical relevance of HRQOL differences among patient groups according to previously published guidelines [47, 48]. The type of missing data generating mechanism will be investigated [49], and sensitivity analysis will be performed to assess the robustness of final results. In addition, the definitive HRQOL deterioration (DD) [50] will be assessed on each EORTC QLQ-C30 scale, based on the corresponding smallest change in the score defining a clinically relevant deterioration [47, 48]. We will also investigate the relationship between satisfaction with information provision and HRQOL outcomes and between preferences and patient characteristics. Statistical significance for all analyses is set as α = 0.05.

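### The stated inputs give 86.9% power at 296 patients, not 90%, and no allowance is shown for the covariate adjustment in the primary fatigue test

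*Protocol article*

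**What the plan says.** The protocol article, section Sample size determination, powers the study to detect "a hazard ratio (HR) of 1.11 for overall survival, for each 10-points increase" on the baseline EORTC QLQ-C30 fatigue scale, "assuming a baseline standard deviation of 29 points". On events it says: "we also assumed a minimum event rate of 35% during the study", with 30 months of follow-up. The result is: "Allowing for an alpha error of 0.05 and a power of 90%, the calculated sample size for this group is 296 patients". An allowance of 5% for patients who are not evaluable takes this to 312. The section names no formula, sidedness, covariates or correlation term.

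The primary question is an adjusted one. The Aims ask whether fatigue predicts survival "independently from other known prognostic factors for OS". The section Primary outcome analysis fits a Cox model "including the baseline fatigue score, the prognostic frailty risk groups and established prognostic factors in MM" and uses a likelihood ratio test for what fatigue adds to the frailty score. The section Secondary outcome analyses closes with: "Statistical significance for all analyses is set as α = 0.05".

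**The concern.** There are two separate problems, and they should not be merged.

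- **The headline figure.** The printed inputs and the printed 296 do not agree at 90% power under a two-sided 5% test.
- **The adjustment.** In an adjusted Cox model, the information on the fatigue coefficient shrinks by the factor 1 − R², where R² is the share of the variance of fatigue explained by the other covariates. This applies whether the hazard ratio of 1.11 is meant as an adjusted or an unadjusted effect. The frailty score is built from age, comorbidity and activities of daily living, so some correlation with self-reported fatigue is to be expected. The sample size section shows no allowance for it.

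The fatigue result decides whether a fatigue-adjusted frailty score is developed. If the real power is nearer 75–85% than 90%, a non-significant result is weaker evidence that fatigue adds nothing to frailty than the stated power would suggest.

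**Working it through.** **Inputs from the article:** hazard ratio 1.11 per 10 points, so b = ln(1.11) = 0.1044 and b² = 0.010891; SD 29 points = 2.9 units of 10 points, so SD² = 8.41; event proportion 0.35; alpha 0.05; power 90%; 296 evaluable patients, so 296 × 0.35 = 103.6 deaths.

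**Inputs assumed:** two-sided alpha, because a likelihood ratio test of one coefficient is a 1-df chi-square test at the stated 0.05; R² of 0.1 to 0.3, because the article gives none.

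**Formulas** (Cox regression with a continuous covariate, Hsieh–Lavori extension of Schoenfeld):

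- Deaths needed: D = (1.960 + 1.2816)² / [SD² × b² × (1 − R²)], with (1.960 + 1.2816)² = 10.507
- Patients needed: N = D / 0.35
- Power at 296: Φ(√[103.6 × 8.41 × b² × (1 − R²)] − 1.960)
- Hazard ratio detectable with 90% power: exp(3.2415 / √[103.6 × 8.41 × (1 − R²)])

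**Attempt to reproduce 296.**

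- Stated inputs, two-sided, R² = 0: D = 10.507 / (8.41 × 0.010891) = 114.7 deaths and N = 114.7 / 0.35 = 327.8, so 328. With 5% not evaluable, 328 / 0.95 = 345.3, so 346.
- Stated inputs, one-sided, R² = 0: N = 267.1, so 268.
- Two-sided, R² = 0, with 0.11 used as the coefficient in place of ln(1.11): N = 10.507 / (8.41 × 0.0121 × 0.35) = 295.02, so 296. A coefficient of 0.11 is a hazard ratio of exp(0.11) = 1.116, not 1.11.
- One-sided, hazard ratio 1.11, R² = 0.10: N = 296.8, so 297.

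The last step does reproduce: 296 / 0.95 = 311.6, so 312.

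**Power at 296 with the stated hazard ratio, R² = 0:** √(103.6 × 8.41 × 0.010891) = 3.080, and Φ(3.080 − 1.960) = 86.9%.

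**With adjustment** (296 evaluable, 35% deaths, two-sided):

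| R² (assumed) | Power, HR 1.11 | Power, coefficient 0.11 (HR 1.116) | HR detectable with 90% power | Evaluable N for 90% at HR 1.11 |
|---|---|---|---|---|
| 0 | 86.9% | 90.1% | 1.116 | 328 |
| 0.1 | 83.2% | 86.9% | 1.123 | 365 |
| 0.2 | 78.7% | 82.7% | 1.131 | 410 |
| 0.3 | 73.1% | 77.5% | 1.140 | 469 |

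**Death rate that would restore 90%** at 296 patients and hazard ratio 1.11 (D / 296): 114.7 / 296 = 39% at R² = 0; 127.5 / 296 = 43% at R² = 0.1; 143.4 / 296 = 48% at R² = 0.2.

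**The case against.** The strongest objections are these.

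- **A reader might infer that the 90% was calculated with fatigue as the only predictor.** The article does not say so. With R² = 0, the stated inputs give 328 two-sided or 268 one-sided, not 296. Of the two routes that come close, one has R² = 0 but replaces ln(1.11) by 0.11; the other keeps the hazard ratio of 1.11 and already contains R² = 0.10, but is one-sided. The article cannot settle which was used, if either. This objection stands. It does not rescue the 90%, because a one-sided calculation does not describe the planned likelihood ratio test: two-sided at R² = 0.10, 296 patients give 83.2%.
- **A reader might put the whole shortfall down to adjustment.** That would be wrong. The fall from 90% to 86.9% is present at R² = 0 and comes from the mismatch between 296 and the hazard ratio of 1.11. Only the further fall is due to adjustment.
- **A reader might conclude that power is below 90% for every positive R².** The 35% is called a minimum event rate, and the death rates worked out above would bring power back to 90%. So the shortfall holds at the stated rate, not at every possible rate.
- **An article may leave the formula and the R² to the full protocol.** That is fair for the omissions alone. But the article prints its inputs and its answer, and these disagree under the planned test, whatever the full protocol adds. A positive R² makes the two-sided disagreement larger.

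**Conclusion.** The 90% is wrong as written for the primary test. With the article's own inputs and a two-sided 5% test, 296 evaluable patients give 86.9% power without adjustment. That the planned test is adjusted is certain from the text; how much power this costs is not, because no R² is given. Over an assumed 0.1 to 0.3, power is 83.2% to 73.1% at a hazard ratio of 1.11, or 86.9% to 77.5% on the more favourable reading that the calculation used a coefficient of 0.11.

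The conclusion rests on two-sided testing, 35% deaths and the standard variance-inflation approximation. It does not establish which calculation was actually run, nor that the cohort has to be enlarged.

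**What to change.** In Sample size determination:

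1. Reconcile 296 with the hazard ratio of 1.11: either correct the stated power to what 296 patients deliver, or state the hazard ratio (about 1.116) to which 90% corresponds before adjustment.
2. State the sidedness and the R² assumed for the adjusted model.
3. Restate the power and the detectable adjusted hazard ratio at 296 evaluable (312 enrolled) over a range of R², such as 0.1, 0.2 and 0.3, and show how they change if deaths exceed 35%.
4. Update R² by regressing baseline fatigue on the frailty groups and the other planned covariates once baseline data are in. This uses no survival outcomes.

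The change is wording and a short table. It needs no extra patients. The price is a less favourable stated power.

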#### Primary outcome analysis

The primary HRQOL objective is to investigate the prognostic value on overall survival of baseline self-reported EORTC QLQ-C30 fatigue scale ratings, independent from the clinically-based prognostic frailty score [6]. Differences between groups will be assessed using χ2, Fisher’s exact, Wilcoxon Mann-Whitney and Kruskall-Wallis tests. We will investigate the prognostic value of baseline variables by Cox proportional hazards regression analysis, including the baseline fatigue score, the prognostic frailty risk groups and established prognostic factors in MM. An extended Cox model will account also for possible time-varying confounding factors (e.g. type of treatment). We will use the likelihood ratio test to assess the prognostic information possibly provided by fatigue, in addition to the prognostic frailty score, by the likelihood ratio test. The robustness of final findings will be assessed by a bootstrap re-sampling procedure [45, 46]. Conditional to the actual prognostic value of the fatigue scale, we will develop a fatigue-adjusted prognostic frailty score included in this scale.

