### Rationale and clinical significance

The choice of treatment for MM patients has been traditionally focused on chronologic age and performance status, as surrogate markers for frailty [5]. Predicting outcomes in this population is critical and recent data has pointed out the limitations of traditional prognostic indicators, by emphasizing the role of geriatric assessment [6]. Palumbo and colleagues [6] demonstrated that geriatric assessment (i.e., the Katz Activity of Daily Living [ADL] [7], the Lawton Instrumental Activity of Daily Living [IADL] [8] and the Charlson Comorbidity Index [CCI] [9]) adds independent prognostic information for risk of death, progression, adverse events and treatment discontinuation regardless of type of therapy and the International Staging System (ISS) in newly diagnosed MM patients. Based on this key finding, Palumbo and colleagues developed the frailty score system [6] which combines factors such as age, comorbidities, cognitive and physical conditions of patients. Importantly, the International Myeloma Working Group (IMWG) proposed this score for the measurement of frailty in the treatment decision-making process thus widely supporting its use in routine practice (http://imwg.myeloma.org).

Although this important evidence indicates the need to enlarge the spectrum of prognostic factors that are considered relevant in MM patients, the frailty score does not include PROs, so as defined by the US Food and Drug Administration (FDA) [10]. A novel finding in the science of prognostication in oncology has been the evidence that PROs, such as symptoms or functional limitations, could also provide prognostic information for survival or other clinical outcomes in patients with advanced disease [11, 12].

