Therefore, based on this compelling evidence stemming from the scientific literature, we will primarily investigate the prognostic value of baseline PROs for overall survival, beyond the frailty score [6], to possibly devise a patient-centric frailty score for RRMM patients. Although the frailty score was developed in newly diagnosed (elderly) patients enrolled in RCTs, and we are aware of the differences with the population that we will be enrolled in our study, it is possible that the prognostic value of this score might also hold true in a population that, per se, is even more frail than the study in which this score was developed [6]. The identification of PROs with independent prognostic value in RRMM has the potential to provide a strong rationale for a more patient-centric approach in routine practice. For example, it would greatly support the inclusion of a standard PRO assessment at the time of deciding type of salvage therapy. Based on previous findings in MM patients [13, 14] and in patients with other advanced hematologic malignancies [15], self-reported fatigue will be regarded as the primary outcome for prognostic factor analyses in this study. Furthermore, in a second instance, other PROs will also be investigated to determine whether they provide more accurate prognostic information than fatigue.

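### The fatigue test is framed against the frailty score but the Cox model adjusts for frailty risk groups, which can leave residual frailty for fatigue to pick up

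*Protocol article*

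**What the plan says.** The Primary outcome analysis section names the frailty adjuster three times, in two forms.

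- Objective: the prognostic value of baseline fatigue "independent from the clinically-based prognostic frailty score".
- Cox model: covariates "including the baseline fatigue score, the prognostic frailty risk groups and established prognostic factors in MM".
- Likelihood ratio test: used "to assess the prognostic information possibly provided by fatigue, in addition to the prognostic frailty score".

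The Rationale section also speaks of the score: "we will primarily investigate the prognostic value of baseline PROs for overall survival, beyond the frailty score". The Aims section is broader and asks for prediction of survival by fatigue "independently from other known prognostic factors for OS".

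The score is described as one "which combines factors such as age, comorbidities, cognitive and physical conditions of patients". The article gives neither its range nor the number or cut-points of the groups. It does not say whether the groups are simply the form in which the score is applied, or which form is in the reduced model of the test. ADL, IADL, the Charlson index and date of birth are recorded on the Baseline History CRF, and data sufficient to compute the score are an inclusion criterion, so either form can be fitted.

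**The concern.** The primary claim is one of independence: fatigue must add something that frailty does not already carry. A model with risk groups treats all patients in a group as equally frail. The score is built from age, comorbidity and physical and cognitive condition, which fatigue can plausibly track. Any frailty difference that remains inside a group and affects survival is then available to the fatigue term. The bias runs towards the study's hypothesis.

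The planned bootstrap does not protect against this, because resampling a model with residual confounding reproduces the confounding. The result also carries forward. The fatigue-adjusted frailty score is conditional on it, and the Secondary outcome analyses section repeats the analysis for the remaining QLQ-C30 and MY20 scales. Those include physical functioning, which lies closer still to the content of the frailty score.

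**Working it through.** The plan states no figure for the frailty adjustment, so there is nothing of its own to reproduce on this point.

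**Inputs from the article (Sample size determination).** 296 evaluable patients, 35% deaths over 30 months, fatigue SD 29 (2.9 units of 10 points), target HR 1.11 per 10 points, alpha 0.05. Expected deaths: 296 × 0.35 = 103.6.

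**Assumptions, not in the documents.** An integer score from 0 to 5, grouped as 0 / 1 / 2 or more; the score's distribution; its hazard ratio; its correlation with fatigue; and no fatigue effect once the score is known. The runs below contain no other prognostic factors unless stated.

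**Mechanism by hand.** Take score shares of 40/30/15/9/4/2%.

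- Mean = 0.30 + 0.30 + 0.27 + 0.16 + 0.10 = 1.13. Variance = 2.85 − 1.13² = 1.573.
- Only the top group (30% of patients) varies internally. Its mean is 0.83/0.30 = 2.767 and its variance is 2.55/0.30 − 2.767² = 0.846.
- Variance left within groups = 0.30 × 0.846 = 0.254, or 0.254/1.573 = 16% of the total.
- Take correlation 0.5 and score HR 1.8 per SD, with the score scaled by 1.2 points as in the simulation. Within-group scaled variance = 0.254/1.44 = 0.176. Covariance with fatigue = 2.9 × 0.5 × 0.176 = 0.255. Fatigue variance within groups = 8.41 × (0.25 × 0.176 + 0.75) = 6.68.
- Spurious log-HR ≈ ln(1.8) × 0.255/6.68 = 0.588 × 0.0382 = 0.0225, so HR ≈ 1.023 per 10 points.

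This is a crude lower guide. Deaths concentrate in the top group, where all the leftover variation sits, and the simulation of this setting gave 1.035.

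**Simulation, same shares (1,500 runs per setting), correlation 0.2 to 0.5, score HR 1.3 to 1.8 per SD.**

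| Adjuster | Fatigue HR per 10 points | False-positive rate |
|---|---|---|
| Risk groups | 1.006 to 1.035 | 5.4% to 15.9% |
| Full score | about 1.00 | 4.3% to 5.6% |

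**Simulation with more patients in the top group (1,500 runs per setting), score HR per point.** False-positive rates:

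| Top group | HR | Correlation | Groups | Full score |
|---|---|---|---|---|
| 40% | 1.3 | 0.3 | 5.5% | 4.6% |
| 40% | 1.3 | 0.5 | 7.9% | 5.2% |
| 40% | 1.5 | 0.3 | 7.8% | 4.4% |
| 40% | 1.5 | 0.5 | 13.0% | 5.1% |
| 60% | 1.3 | 0.3 | 6.9% | 5.0% |
| 60% | 1.3 | 0.5 | 13.5% | 4.7% |
| 60% | 1.5 | 0.3 | 9.3% | 4.3% |
| 60% | 1.5 | 0.5 | 21.6% | 5.2% |

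The spurious HR in this set was 1.01 to 1.05.

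**Hazard flat within groups** (assumed relative hazards 1 / 1.5 / 2.5, 1,000 runs): group adjustment rejected in 3.2% to 5.7%, with HR about 1.00. There is no inflation here.

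**One further covariate, correlated 0.6 with the score:** rejection under group adjustment fell from 25% to 19% in one steep setting and from 15% to 12% in another. The inflation shrank but did not vanish.

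**Scale against the design effect.** ln(1.035)/ln(1.11) = 0.0344/0.1044 = 0.33. ln(1.05)/ln(1.11) = 0.0488/0.1044 = 0.47.

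**The case against.** The strongest reply is that there is no conflict: the risk groups are naturally read as the categories that the score yields. If the tool is used in practice as groups, adjusting for them tests added value over the tool as used, and risk captured within a group is exactly the added information sought. Much of this stands. The documents do not show that score and groups are rival adjusters. But the Aims section asks for independence from known prognostic factors generally, which is more than added value over a grouped tool. If groups are meant, a fatigue effect could still consist of information already held in the collected score.

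Second, simulations that generate hazard from the score make group adjustment wrong by construction. That is correct, and with hazard flat within groups the inflation disappears. The lowest simulated rate, 5.5%, has a Monte Carlo standard error of about 0.6% and cannot be told from 5%.

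Third, the planned model contains other prognostic factors that may absorb part of the residual. This also stands, although they are unnamed and their effect cannot be relied on.

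Fourth, covariate coding is often left to an analysis plan. Here, however, the article does name a form in its covariate list, and it differs from the form in the objective and the test.

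A reader might also infer from the description of this cohort as "a population that, per se, is even more frail than the study in which this score was developed" that patients will crowd into the worst group, where grouping loses most. The documents do not support that as fact. The same sentence says the score was developed in elderly patients, whereas this study enrols from age 18 and excludes recent grade 3 or higher events, more than five prior lines, and major cognitive dysfunction hampering consent. The distribution of frailty is unknown.

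**Conclusion.** The point holds in conditional form. The objective and the test refer to the score, the model refers to groups, and the nested models are not tied to either. If mortality varies with frailty inside groups and fatigue follows that variation, adjustment for groups alone biases the fatigue effect upwards.

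Under the assumed inputs the false-positive rate lies between about 5% and about 20%. The steepest settings gave 16% to 25%, depending on the assumed score distribution, before allowing for other covariates. The spurious HR reaches 1.035 to 1.05 per 10 points, a third to just under half of the design effect on the log scale.

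A reader might infer that the type I error of the primary test exceeds 0.05. The documents do not support that flat statement: it depends on a score range, cut-points, a within-group hazard gradient and a correlation that they do not give. What favours a change is that adjusting for the full score, alone or with the groups, kept the rate at about 4% to 6% and the HR at 1.00 whether or not hazard was flat within groups. This is a cheap improvement, not a demonstrated error.

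**What to change.** In Primary outcome analysis, state one set of frailty terms and use it in the Cox model and in both the reduced and the full model of the likelihood ratio test. That set should include the uncollapsed frailty score, or its collected components (age, ADL, IADL, Charlson index), alone or alongside the risk groups, together with the established prognostic factors. Report the model with risk groups only as a secondary analysis for clinical presentation.

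No new data are needed. If there are three groups (2 degrees of freedom), a linear score in their place uses one fewer, the score added to the groups uses one more, and four linear components in their place use two more. Adding all four components to the groups would use four more, so the leaner options are preferable. Against about 104 expected deaths, one or two extra terms are a small cost. The other possible price is a slightly smaller fatigue estimate.
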